#### Child-focused intervention

The child-focused intervention approach focuses primarily on remediation of *body function and structure *as the starting point of intervention. The task analysis focuses on constraints and facilitators in the child. Therapeutic techniques will be used to improve the child's body functions and structure, such as strength, coordination, balance, quality of movement, and range of motion. Strategies, focusing on remediation of body function and structure, can be performed in isolation or as part of practicing activities. The therapist is the primary decision maker in the intervention.

In the training therapists will learn child-focused intervention principles. Therapists will be instructed to achieve the goals primarily through changing the components of body function and structure within the child.

#### Context-focused intervention

The context-focused intervention approach focuses primarily on changing constraints in the environment or task as the starting point of intervention. The task analysis focuses on constraints and facilitators in the environment and the task. For young children with CP (2-3 years) the most important contextual factors are situated in the home environment. In this approach therefore, the home environment is taken into consideration [34], and there is a strong collaboration between therapists and parents recognizing parents' role as advocates and decision makers for their child [35,36]. In this approach, the task of the therapist is not to elicit specific responses by handling the child, but to provide an environment which enables the child to learn to perform self-initiated actions within naturally occurring restraints.

In the training the therapists will learn the context-focused intervention principles. Therapists will be instructed to achieve the goals primarily through changing the environment and tasks. Therefore, the therapists will challenge the children with frequent and varied practice within the context of daily activities and routines.

#### Regular care

The regular care intervention in this study will be like the intervention the children received before participating in the study and continues throughout the study period. Regular care consists probably of a mixture of child-focused intervention approaches and context-focused intervention approaches, with the balance between child-focused and context-focused approaches based on the individual therapist's view.

### Study parameters

#### Primary study outcome

The primary outcome of the study will be the capability of functional skills in mobility and self-care using the Functional Skills Scale of the PEDI *(PEDI-FSS*;[37]). The PEDI is a standardized assessment instrument using parental reports through structured interview, and consists of the Functional Skills Scale (FSS), and the Caregiver Assistance Scale (CAS), both consisting of three domains: self-care, mobility, and social function. For the purpose of the present study the self-care and mobility domain will be used. The PEDI-FSS assesses what a child can do in his/her daily environment. Each question is scored as positive (score 1) or negative (score 0). A positive score is given when the child is capable of accomplishing the activity. The Dutch adaptation and translation of the PEDI, the PEDI-NL[38], which has good psychometric properties, will be used [39].

#### Secondary study outcomes

Performance of mobility-related activities and self-care-related activities will be measured by the *Caregiver Assistance Scale of the PEDI (PEDI-CAS*;[37]). This scale measures the level of caregiver assistance a child receives to accomplish the activities. It concerns the child's actual behavior in his or her daily environment.

To set intervention goals and to measure the amount of successfully reached goals after the six months study-intervention period the *COPM *will be used [32]. The COPM is an individualized measure designed to detect problems in various areas of daily functioning and to assess changes in self-perceived performance and satisfaction over time through a semi-structured interview. The COPM has robust psychometric properties for use in a pediatric clinical trial [40]. The Dutch version of the COPM has shown good validity [41,42].

Capacity of motor skills will be assessed with the *Gross Motor Function Measure (GMFM*;[43]). The GMFM is a standardized observational instrument that has been developed to measure the gross motor function in children with CP in a specific test situation, without the use of mobility aids or orthosis. The original GMFM consists of 88 items grouped into five dimensions of gross motor function: lying and rolling; sitting; crawling and kneeling; standing; and walking, running, and jumping. There is also a 66-item version of the GMFM available, in which 22 items of the GMFM-88 are removed, many of them in the dimension of lying and rolling. The most recent development with the GMFM is the GMFM-66-IS (Item-Set) in which four items sets are used to determine which items need to be examined. This abbreviated version of the GMFM is less time consuming and has shown to be valid en reliable [44]. In the present study, with a study population of children with CP aged 2 to 3 years, we expect that the lying and rolling and sitting dimensions can provide essential information. Therefore all items of these two dimensions of the GMFM-88 will be assessed. In addition the GMFM-66-IS will be used to determine which items on the other dimensions need to be examined for each individual child. The Dutch translation of the GMFM-88, which has good psychometric properties comparable to those of the original GMFM will be used [45,46].

Participation of the child in daily life activities will be measured by the *Preschool Children's Assessment of Participation and Enjoyment (Pre-School CAPE)*. The Pre-school CAPE is a measure based on the CAPE (Children's Assessment of Participation and Enjoyment) [47]. The CAPE is a self-reported 55-item questionnaire to measure participation and enjoyment in children 6 to 21 years of age. The CAPE has shown to be sensitive in measuring change in participation during intervention [48] and shows good psychometric properties [35,49]. The CAPE was adapted for children at a younger age to the Pre-school CAPE by changing some items and parents will fill in the questionnaire for their children. This questionnaire consists of 48 items to measure the participation in everyday activities in children over the past four months. The Pre-school CAPE measures on five domains: play activities, skill development, active physical recreation, social activities and other activities. The questionnaire provides information on the diversity and intensity of these activities.

Parental perception of the participation of the family will be measured by the *Family participation questionnaire*. In a semi-structured interview parents are asked three questions on daily activities of the family, and on family participation. The questionnaire has shown shows good inter-rater reliability in the PERRIN CP 0-5 study[50].

Quality of life of the child will be measured by *TNO-AZL Preschool Children Quality of Life Questionnaire (TAPQOL*;[51]). The TAPQOL is a 43-item questionnaire to measure parents' perception of the health-related quality of life in preschool children. Parents fill in the questionnaire as a proxy for their child. The questionnaire consists of 12 scales on the domain of physical, social, cognitive and emotional functioning. The occurrence of these items is assessed and at some items also the wellbeing of the child in relation to the item is scored. The TAPQOL showed to have a good reliability [51,52].

Quality of life of the parents will be measured by three questions based on a national survey of 'Statistics Netherlands', the *Questions Quality of Life*. The answers of these questions can be compared with Dutch norms.

Parental stress in relation to raising their child will be measured by the *Nijmeegse Ouderlijke Stress Index - Kort (NOSI-K*;[53]). The NOSI-K is with 25 items the short version of the NOSI, which is a Dutch adaptation of the Parenting Stress Index (PSI). The NOSI-K has shown good psychometric properties [53].

The empowerment of the family will be measured by the *Family Empowerment Scale (FES*;[54]). The FES is a 34-item questionnaire to measure empowerment in families of children with emotional, behavioral or mental disorders. The FES consists of three domains about family, child's services, and parents' involvement in the community. The FES has good psychometric properties [54,55].

The family-centeredness of care as rated by the parents will be measured by the *Measure of Processes of Care (MPOC*;[56]). The MPOC is a 56-item questionnaire to assess the extent to which parents perceived the family centeredness of the health care their child received in the past year. The questionnaire consists of five scales; enabling and partnership, providing general information, providing specific information about the child, coordinated and comprehensive care for the child and family, and respectful and supportive care. The occurring of these items will be assessed as well as how important they are to parents. In this study the Dutch version of the MPOC will be used, with good psychometric properties [57].

The family-centeredness of care as rated by professionals will be measured by the *Measure of Processes of Care for service providers (MPOC-SP*;[58]). The MPOC-SP is a 27-item questionnaire to assess to which extent the care that service providers provided the past year was family-centered. The questionnaire consists of four scales. In this study the Dutch version of the MPOC-SP will be used, with good psychometric properties [58,59].

#### Other study parameters

Based on the literature, it is assumed that some child- and family variables might be important in explaining effects in different groups. Therefore, the following variables will be registered systematically, and will be analyzed as potential determinants:

The gross motor ability level of the child will be classified by the *GMFCS *[29,30]. The GMFCS is a classification system based on the self-initiated movements of the child. The system consists of a 5-level ordinal scale, which describes differences in severity of mobility abilities. Level I represents the best gross motor function, level V the least. The GMFCS shows good psychometric properties [29,30].

Manual skills will be classified by the *Manual Ability Classification System (MACS*; [60]). The classification system consists of five levels, from level I 'Handles objects easily and successfully' to level V 'Does not handle objects and has severely limited ability to perform even simple actions'. The MACS has shown good reliability in children 2-5 years of age [61]. Validity of the MACS was shown in children 4-18 years of age [60]. The validity in children 2-5 years of age has not been studied yet.

Type of CP will be classified according to *Surveillance of Cerebral Palsy in Europe (SCPE) - guideline *[62]. This guideline classifies CP in the subtypes of spastic, dyskinetic, or ataxic. Also the topographical distribution is classified in children with spastic CP; unilateral involvement (hemiplegia) versus bilateral involvement (diplegia, tetraplegia).

Cognitive functioning of the child will be measured by the *Bayley Scales of Infant Development-Second edition (BSID-II) - Mental Scale*, with good psychometric properties [63].

Coping style of the parents will be measured by the *Utrechtse Copinglijst (UCL)*, a Dutch 47-item questionnaire to determine how parents handle problems and events in daily life, with sufficient psychometric properties [64].

*Session documentation *of the therapists will be collected. Therapists in the child-focused intervention approach and in the context-focused intervention approach group will document on special forms and will send in their documentation during the intervention period to control the therapist's adherence. Experience from previous work [31,65,66] has shown that therapists are able to implement treatment protocols in a reliable and valid manner. Therapists in the regular care intervention group will not receive instructions on documentation and will document the way they are used to do. Their documentation will be collected after the end of the study. Therapists in all groups will videotape one session of each child at four months of study-intervention. These tapes will be evaluated by trained raters, for procedural reliability and to describe regular care intervention.

Additional data on the working mechanisms will be collected by *in-depth interviews *with the families. Parents of children in the child-focused intervention approach and context-focused intervention approach group will be interviewed after the six months study-intervention period. Questions will be on parents experiences with the interventions, to get more insight into the advantages and disadvantages of the interventions. We expect that an 'informational redundancy'-effect will occur after interviewing half of the parents. To prevent that parents will be interviewed unnecessary, not all parents will be interviewed.

### Data analysis

Descriptive statistics including frequencies, means, standard deviations, and for nonparametric data medians and interquartile ranges will be calculated. Data will be analyzed based on an intention to treat-analysis. The effects of the three interventions will be evaluated using repeated-measures analysis of variance (group[3] × time[2]) with the outcome measures as the dependent variable. In case of a statistically significant interaction group × time effect, post-hoc analyses will be performed to determine between which groups the differences occur. To assess the effects during and after the six month study-intervention period, repeated-measures analysis of variance (group[3] × time[3]) with repeated contrasts will be used, with the same outcome measures.

To explore variables that might be related to the efficacy of the intervention, and that might explain possible variability between children, multiple regression analyses will be performed. The change scores on the PEDI-FSS will be the dependent variable, and the classification of gross motor abilities, classification of manual abilities, cognition of the child and coping style of the parents will be analyzed as independent variables.

The interviews with the parents on their experiences with the interventions, and therapists' preferences for intervention will be analyzed using qualitative analyses.

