### Sample size

Sample size was calculated for the Pediatric Evaluation of Disability Inventory (PEDI) (based on data from an earlier study [31]; with a subgroup analysis of children of 2-3 years) using the following assumptions in a one-way analysis of variance power analysis (based on a power of 80% and a two-sided α-value of 0.05). An estimated difference in the change scores between the context-focused intervention approach group and the regular care intervention group of 4.5 points (SD = 6.0) on the PEDI. Sigma for the three groups = 2.1. Taking into account the clustered nature of the sample of participating children a correction will be used, based on an average cluster size (number of children per therapist) of 2, and an ICC of 0.1. These specifications lead to a required total sample size of 85. Expecting a 10% drop-out in total 94 children will be recruited for the present study.

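### The only efficacy model named, classical repeated-measures ANOVA, does not as usually run keep every enrolled child, so it sits badly with the stated intention-to-treat principle

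*Protocol article*

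**What the plan says.** All statements are in the protocol article.

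- **Principle (Data analysis):** "Data will be analyzed based on an intention to treat-analysis".
- **Main model (Data analysis):** "The effects of the three interventions will be evaluated using repeated-measures analysis of variance (group[3] × time[2]) with the outcome measures as the dependent variable". The two time points are not named; I read them as T0 (baseline) and T1 (six months).
- **Second model (Data analysis):** for effects during and after the intervention period, "repeated-measures analysis of variance (group[3] × time[3]) with repeated contrasts will be used, with the same outcome measures".
- **Expected loss (Sample size):** "Expecting a 10% drop-out in total 94 children will be recruited for the present study". When the loss is expected to occur is not stated.
- **Visits and allocation (Study procedures):** T0, T1 after six months, and T2 three months later. Therapists are randomised, and each child is in the arm of his or her therapist.

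The article gives no rule for missing outcomes: no imputation and no likelihood-based model, but also no restriction to completers.

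**The concern.** The article fixes both a principle and a method, and as usually run the method does not deliver the principle. Classical repeated-measures ANOVA works on complete outcome vectors, so a child with one value missing contributes nothing to that model.

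Two consequences follow. First, the primary comparison may rest on fewer than all enrolled children, although intention to treat is promised. Second, the T0-T1 effect is estimated twice. Repeated contrasts compare adjacent time points, so the first contrast of the three-time model is again T0 to T1. With complete data the two answers agree. Once any child has T1 but not T2, they come from different children.

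Drop-out related to progress is plausible here, though not shown. Context-focused care involves parents in goals, sub-goals and evaluation (Table 1) and relies on close work with the family at home, whereas regular care continues unchanged. The primary outcome is a parent interview (Primary study outcome), so a family that disengages takes the outcome with it.

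**Working it through.** **1. The plan's own sample size.** Inputs from Sample size: "based on a power of 80% and a two-sided α-value of 0.05"; "regular care intervention group of 4.5 points (SD = 6.0) on the PEDI"; "Sigma for the three groups = 2.1"; two children per therapist, ICC 0.1.

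- Design effect: 1 + (2 - 1) × 0.1 = 1.1.
- Group means of 0, 0 and 4.5 have a standard deviation of 2.12, matching the stated 2.1. Then f² = (2.12/6.0)² = 0.125.
- The large-sample noncentrality for 80% power with 2 degrees of freedom is 9.635. So N = 9.635/0.125 = 77.1, and 77.1 × 1.1 = 84.8, i.e. 85. The stated figure is reproduced.
- Drop-out: 85 × 1.1 = 93.5, i.e. 94 (85/0.9 = 94.4 would round up to 95).

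So 80% power is planned on about 85 children with usable outcomes. The same inflation would be made under any model and any analysis set.

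**2. Who stays in each model, if nothing is imputed.**

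| Values available | group[3] × time[2] | group[3] × time[3] | Mixed model |
|---|---|---|---|
| T0, T1, T2 | in | in | in |
| T0, T1 | in | out | in |
| T0, T2 | out | out | in |
| T0 only | out | out | in, with little information on change |

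**3. How many.** 94 × 0.10 = 9.4, about 9 children. If the 10% covers the whole study to T2, up to 9 are missing from the two-time model and about 9 from the three-time model. If the 10% is lost by T1, about 9 leave both models and any later loss comes on top in the three-time model.

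**4. Power by number analysed** (design effect 1.1; first figure large-sample with f² = 0.125, second exact noncentral F with f = 0.35):

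| Analysed | Power |
|---|---|
| 94 | 84% / 82% |
| 85 | 80% / 78% |
| 80 | 78% / 75% |
| 76 (19% lost, an assumption) | 75% / 72% |

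Power at the planned loss is close to target, so precision is not the main issue. The mixed model would not reach the 94-child row either, because a child with T0 only says little about change.

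**5. Bias, as an assumption only.** Let p be the fraction of an arm without T1, and D the mean change of completers minus that of drop-outs. The completer mean exceeds the full-arm mean by p × D, so the contrast between two arms is biased by p₁D₁ - p₂D₂. With the same D in both arms:

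| Difference in drop-out | D = 2 | D = 4.5 | D = 6 |
|---|---|---|---|
| 0 points | 0 | 0 | 0 |
| 10 percentage points (e.g. 15% v 5%) | 0.2 | 0.45 | 0.6 |
| 20 percentage points (e.g. 20% v 0%) | 0.4 | 0.9 | 1.2 |

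Against the planned 4.5 points, 0.6 is 13% and 1.2 is 27%. The document gives neither p by arm nor D. If D = 0 in each arm, the bias is zero even when drop-out rates differ.

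**The case against.** The strongest reply is that this is only a missing-data rule that a condensed article may leave to the full protocol or analysis plan. Listwise deletion is the usual behaviour of the method, not something the article states. Imputation before the ANOVA would fit every word, and intention to treat in its basic sense, analysis by allocated arm, is compatible with ANOVA. This stands: there is no express contradiction, and the silence on missing values is not itself the point. What remains is that the article commits to a specific model when a better one is available at almost no cost.

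A reader might infer from the step between 85 and 94 that a completer analysis is planned. The document does not support that: the step is ordinary drop-out inflation and says nothing about who is analysed. Nor does the plan lose every child with a missed visit, since a child missing only T2 stays in the two-time analysis.

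Arm-related drop-out is also limited by design. All arms share one visit schedule and at least 18 sessions, the extra training is for therapists rather than families, and parents who foresee that they cannot adhere are not entered (Study population). This lowers the risk without removing it.

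Finally, a mixed model does not cure drop-out that depends on the unobserved T1 value. That is correct and limits what the change can achieve.

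**Conclusion.** The point holds in a limited form. As usually run, the named model sits badly with the stated intention-to-treat principle when 10% drop-out is expected, and it can produce two T0-T1 estimates from different children. About 9 of 94 children are at issue, with the split between T1 and T2 unknown. The size of any bias cannot be taken from the document; the 0 to 1.2 points shown rest wholly on assumed drop-out patterns.

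The conclusion assumes that the two-time model means T0 and T1 and that no imputation is done. It is a nearly free improvement to a stated method, not evidence that the planned analysis is biased or that completers only will be analysed.

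**What to change.** Replace both ANOVAs with one likelihood-based linear mixed model:

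- all enrolled children, in the arm of the therapist assigned at entry, with every available T0, T1 and T2 value;
- categorical time, group and group × time, with unstructured within-child covariance;
- a therapist random effect, to match the clustering assumed in the sample size. It should be allowed to act on change, because a therapist effect that is constant over time cancels from a within-child difference;
- the T0-T1 arm contrast as primary and the T1-T2 contrast as secondary.

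This gives one T0-T1 estimate and uses T1 values of children who miss T2. It relaxes the missing-data assumption to missing at random, so loss explained by observed baseline or T1 values is accommodated. Drop-out that depends on unobserved outcomes would still bias it. If the ANOVAs are kept, stated multiple imputation would be an acceptable way to reconcile them with intention to treat.

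The cost is analysis wording only, settled before the data are analysed; no extra children, visits or measurements are needed.

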### Study procedures

The three interventions arms will be distributed within a centre. The physical and occupational therapists who agreed to participate will be randomized in one of the three intervention arms by block randomization, with a block size of six. Children will follow their therapist into the intervention group that the therapist was assigned to. The therapist who provides the study intervention to the child will be the prime therapist for the children during the six months study-intervention period. Furthermore, the prime therapist is the one who will document on the session documentation, will set goals with parents and is the contact person for the researchers. The other therapists who treat the child will be available for expert information consultation. Therapists can participate in the study with a maximum of two children at the same time and with a maximum of four children overall in the study. We expect an average of two children per therapist.

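### Therapists are randomised and the sample size assumes therapist clustering, but the planned repeated-measures ANOVA treats children as independent, so its error rate is not assured

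*Protocol article*

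**What the plan says.** Under Study procedures, the participating therapists are the unit of allocation: those "who agreed to participate will be randomized in one of the three intervention arms by block randomization, with a block size of six". The children are not randomised themselves: "Children will follow their therapist into the intervention group that the therapist was assigned to". A therapist may treat up to four children over the study, two on average, and all three arms are to be present within a centre.

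The Sample size section recognises this: "Taking into account the clustered nature of the sample of participating children a correction will be used", with an "average cluster size (number of children per therapist) of 2, and an ICC of 0.1".

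The Data analysis section says the effects of the three interventions will be "evaluated using repeated-measures analysis of variance (group[3] × time[2]) with the outcome measures as the dependent variable". A significant group × time interaction leads to post-hoc comparisons between arms. The three-month follow-up uses the same kind of model with three time points and repeated contrasts. Neither model has a therapist term, a centre term or any other allowance for clustering.

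**The concern.** The article names a specific test, and that test conflicts with both the randomised unit and the non-zero ICC assumed when the trial was sized. The correction under Sample size changes how many children are recruited. It does not change the error term used to judge the result.

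Children treated by one therapist share that therapist's skill and adherence to the approach, so their changes are likely to be positively correlated. Ignoring a positive correlation understates the variance of the arm means. The interaction test is also the gateway to the post-hoc comparisons, so an inflated error rate there passes into statements about which approach works.

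**Working it through.** **Inputs from the article.** Two-sided α 0.05 and power 80%; difference "of 4.5 points (SD = 6.0) on the PEDI"; "Sigma for the three groups = 2.1"; m = 2 children per therapist; ICC 0.1; 85 children required and 94 recruited; about 15 centres.

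**The plan's own figure.**
- Means of 0, 0 and 4.5 have a standard deviation of 2.12, which matches the stated 2.1. So f = 2.12/6.0 = 0.3536.
- With three groups, the large-sample noncentrality for 80% power is 9.635, giving N = 9.635/0.3536² = 77.1.
- The design effect is 1 + (2 − 1) × 0.1 = 1.10, and 77.1 × 1.10 = 84.8, hence 85. With f = 2.1/6.0 = 0.350 the result is 78.7 × 1.10 = 86.5, hence 87.
- For dropout, 85/0.9 = 94.4 and 85 × 1.1 = 93.5; both fit 94.
- The exact F test needs 81 to 84 children before the correction and 89 to 93 after it. The stated 85 therefore contains the correction under the large-sample formula.

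**What the planned test does.** With two time points, the group × time F statistic is the one-way ANOVA F on change scores with between-child error. The repeated contrasts at three time points are also changes between adjacent times, so the same reasoning applies. The ICC that matters is that of change.

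**Size at the plan's values, no centre effect.**
- Naive standard error divided by true standard error: 1/√1.10 = 0.953, about 5% too small.
- Simulated under the null with 14 therapists and 28 children per arm, type I error is about 6.4 to 6.7% (6.6% in the largest run, 200,000 replicates). Pairwise 95% intervals cover about 93.8%.
- With an assumed mix of one to four children per therapist (mean 2, coefficient of variation about 0.47), the design effect is 1 + (2 × (1 + 0.47²) − 1) × 0.1 = 1.14 and type I error is about 7 to 7.5%.
- For other ICCs, also assumed, with two children each: about 5.8% at 0.05, 8.4% at 0.2 and 10% at 0.3.

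**Adding a centre effect on change.** The documents give no centre variance, so the shares of total variance below are assumptions, as is the layout of one therapist per arm in each of 14 centres. The therapist share stays at 0.10.

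| Centre share | Type I error, two children each | Type I error, sizes 1 to 4 |
|---|---|---|
| 0 | 6.4–6.7% | 7–7.5% |
| 0.05 | 5.7–6.0% | 6.4–6.8% |
| 0.10 | 5.0–5.2% | 5.6–6.5% |

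If the assumed ICC of 0.1 were half therapist and half centre, type I error would be about 5%.

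**After a correction.** An ANOVA on therapist means (14 per arm, two children each, ICC 0.1) has a simulated type I error of 5.0%. Its power has noncentrality N × f²/1.10 and denominator degrees of freedom equal to the number of therapists minus 3:
- 85 children, 42 therapists: 75.9% (f = 0.350) to 76.8% (f = 0.3536).
- 94 children, 47 therapists: 80.6% to 81.4%.

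**The case against.** The strongest counter-argument concerns centre. Since arms are spread within centres, a shared centre effect largely cancels from the arm differences but stays in the error term, which makes the planned test conservative. The table shows that a plausible centre share can bring the error close to 5%. This stands. A reader might infer that every p-value will be too small, or that omitting centre is a second fault in the same direction; the documents support neither. The offset does not settle the matter, however. It depends on an unstated variance and on balance within centres. With about 94/2 = 47 therapists in about 15 centres there are roughly three per centre, half a block of six, so exact balance is not guaranteed.

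Two further inferences should be resisted. One is that the moderator regression has the same fault. Its predictors are child and family characteristics, and the analysis is exploratory. At an outcome ICC of 0.1 with two children per therapist, the simulated type I error for one predictor was 5.2% (predictor not clustered) and 4.9% (predictor ICC 0.2), both close to nominal. The other is that the provider-rated care questionnaire (MPOC-SP) will be analysed as if there were 94 respondents. The article nowhere says so.

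It can also be said that an article leaves modelling detail to the full plan. That would answer an omission, but here a particular model is named and it does not fit the design.

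**Conclusion.** The point holds in limited form and should be fixed. The named efficacy analyses ignore the randomised unit. At the plan's own cluster size and ICC, with no centre effect, a nominal 5% test becomes one of about 6.4 to 6.7%, and standard errors are about 5% too small. The inflation is modest at these values and grows with unequal cluster sizes or a higher ICC. Centre variance could offset part or nearly all of it. The figures for unequal sizes, for other ICCs and for centre shares rest on assumptions that the documents neither give nor exclude. What can be said firmly is that the planned test has no assured error rate, not that its results are necessarily too optimistic.

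**What to change.** For the primary and follow-up efficacy comparisons, replace the ANOVA with a linear mixed model, or an equivalent cluster-adjusted analysis, containing:
- group, time and group × time, with child as the repeated unit;
- a therapist effect that acts on change, such as a therapist intercept when later scores are modelled given baseline, or a therapist × time effect. A therapist intercept common to all time points would cancel from the change and correct nothing;
- a centre effect;
- small-sample degrees of freedom (Satterthwaite or Kenward–Roger) that reflect the number of therapists.

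The plan should also say what happens if the therapist variance is estimated at zero. With 42 therapists of two children and ICC 0.1, the estimate is zero or negative with probability P(F(39, 42) ≤ 0.9/1.1) = 0.26. A model confined to non-negative variances then drops the therapist effect. Allowing a negative within-therapist covariance, or analysing at therapist level, avoids this.

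The cost is a reworded analysis section, a record of each child's prime therapist and centre, and slightly wider intervals. Power for a therapist-level test is about 76 to 77% with 85 children and about 81% if all 94 are analysed. Only part of the shortfall at 85 comes from the therapist-level degrees of freedom: the exact F test on 85/1.10 = 77.3 effective children already has only 77.5 to 78.4%. No new outcome data are needed.
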